### Aetiology of venous ulcers

The pathophysiology of venous ulceration is controversial [13] however it is believed that ulcers result from venous occlusion or valvular incompetence and subsequent superficial venous hypertension [14]. Venous leg ulcers occur as a result of underlying venous disease where damage has occurred to the superficial deep or perforating veins. Although aetiology of venous ulceration is unclear, it has been suggested that ulceration results from increased intraluminal pressure in the capillaries. This results in fibrin deposition around the capillaries [15]. White blood cells are activated and release proteolytic enzymes that cause further tissue destruction. The alternative 'Trap' hypothesis proposes that fibrin and macromolecules eventually leak into the dermis where they bind with growth factors, making then unavailable for the tissue repair process.

The most recent theories about pathogenesis of venous ulcer have associated it with microcirculatory abnormalities and generation of an inflammatory response. The molecular and cellular profiles of chronic skin wound wounds are substantially different than found in acute healing wounds. Healing time is influenced by patient age, ulcer duration and ulcer area, but not by type of venous incompetence [15,16]

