### Venous ulcer healing

Venous leg ulcer healing rates vary considerably. In wound centres providing graduated compression bandaging treatment for venous ulcers, healing rates vary from 25 to 50% after 12 weeks to 40% - 70% at 12 weeks [19] and after two years of compression therapy 20% of all chronic venous leg ulcers remain unhealed and even when healing does occur, approximately 56% will recur [3].

There are many reasons for variation in treatment times for venous ulcers. Chronic wounds that measure less than 10 cm^2 ^and are present for less than 12 months at first treatment are likely to be healed in 71% of patients within 24 weeks of treatment [20]. Conversely, chronic wounds that were greater than 10 cm^2 ^and have been present for more than 12 months, had only a 22% likelihood of being healed within the 24 week period. High compression is more effective than low compression but there are no clear differences in the effectiveness of different types of high compression [18].

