### Randomisation

Randomisation will follow a computer generated allocation schedule (NQuery version 7), using allocation concealment to prevent prior knowledge of treatment assignment. Numbers will be assigned in strict chronological sequence and study participants will be entered in sequence. Randomisation in small block sizes (2 and 4) will be stratified by wound clinic site and wound size ≤ 10 cm^2 ^or >10 cm^2 ^(assessed from the wound tracings and digital photography). Each study participant will be allocated a unique randomisation number on successful completion of screening.

Patients will be randomised to receive either control or intervention group using a central computer generated random number generated by using a central computer generated randomisation sequence. The randomization code will be sent to the Investigator (or designee) who will prepare treatments according to the randomisation code.

To decrease bias and confounders the decision to accept or reject a participant will be made using inclusion and exclusion criteria. Informed consent will be obtained from participants prior to obtaining the randomisation code. Independent clinicians will assess the eligibility of the patient, input identifiers on the randomisation website interface to document eligibility and obtain the randomisation number and allocation of bandage type. The compression bandage systems will be applied according to the computer generated list allocation. The codes will only be revealed to the researchers once the recruitment, data collection and wound measurement analysis are completed. The allocation list will be stored within the Clinical Informatics and Data Management Centre of the DEPM.

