The analysis of the primary endpoint will be by z-test and linear regression if the distribution of log (A2/A1) is reasonably symmetric. It is unclear from previous studies whether this will be the case. If necessary the analysis of hypothesis 1 will be by non-parametric Wilcoxon rank-sum test. If major differences are evident in key variables (age, gender, ethnicity, BMI, smoking, ABPI, ankle and calf circumference, range of ankle mobility, past medical history- diabetes, anaemia, hypertension, past surgical history-hip surgery, venous surgery/ligation, DVT, medication history) between allocated groups at baseline, then the baseline values will be included as covariates in a second linear regression model for the primary outcome. Imbalance will be defined as a difference in means (on a log scale for variables following a skewed distribution) of ≥ 0.33 standard deviations or, for binary and categorical variables a relative risk of ≥ 2 (where prevalence is ≥ 10%).

Finally, 18 participants per group need to have wound area assessed at the end of the 12-week follow-up. To allow for loss-to-follow-up of 20% of participants between baseline and follow-up we will randomise 23 participants to each arm.

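### Covariates enter only a second regression, chosen by chance baseline imbalance rather than by the prognostic factors and randomisation strata the protocol itself names

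*Protocol article*

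**What the plan says.** The Sample Size and Analysis plan section analyses log(Area2/Area1) by z-test and linear regression, or by Wilcoxon rank-sum if the distribution is not reasonably symmetric. No covariate is named for that first regression.

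Adjustment comes only through a conditional rule. If major differences in key variables are seen between the arms at baseline, "then the baseline values will be included as covariates in a second linear regression model for the primary outcome". The threshold for continuous variables is explicit: "Imbalance will be defined as a difference in means (on a log scale for variables following a skewed distribution) of ≥ 0.33 standard deviations". For binary and categorical variables it is a relative risk of 2 or more where prevalence is at least 10%.

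The candidates begin with "age, gender, ethnicity, BMI, smoking, ABPI, ankle and calf circumference, range of ankle mobility" and continue with items of medical, surgical and medication history, about 16 in all. Site, wound area and ulcer duration are not among them.

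Elsewhere the protocol says:

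- Randomisation: allocation "will be stratified by wound clinic site and wound size", cut at 10 cm².
- Aetiology of venous ulcers: "Healing time is influenced by patient age, ulcer duration and ulcer area".
- Venous ulcer healing: 71% healed within 24 weeks if the ulcer was under 10 cm² and under 12 months old. Ulcers that were both larger and older "had only a 22% likelihood of being healed within the 24 week period".

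**The concern.** Baseline covariates in a randomised trial are worth adjusting for because they predict the outcome. An observed imbalance between randomised arms is a chance event and says nothing about prognosis. A rule that selects on imbalance brings in whichever variables happen to differ, prognostic or not, and those are the ones most correlated with treatment in that sample, so they cost precision. The factors that the protocol itself calls prognostic stay out: area and duration cannot enter under the printed rule, and age enters only if it happens to be imbalanced.

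Three things are at stake:

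- The adjusted model's content is not known in advance, although its thresholds are.
- The randomisation is stratified, but no adjustment for the strata is named. If the strata predict outcome, the standard error is larger than the design warrants.
- Two estimates will usually be available, and the plan does not say which one carries the conclusion if they disagree.

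**Working it through.** **The plan's own figures.** Inputs from Sample Size and Analysis plan: difference ln(0.8) − ln(0.5) = 0.47, SD 0.5, two-sided alpha 0.05, power 80%, 20% loss.

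- n per arm = 2 × (1.96 + 0.8416)² × (0.5/0.47)² = 17.8, so 18.
- 18/0.8 = 22.5, so 23 randomised per arm.
- Power at 18 per arm is 80.5% by normal approximation and 78% on the t distribution with 34 degrees of freedom.

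Both stated sample sizes are reproduced.

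**Chance of a trigger, continuous variable.** Under randomisation the difference in means has standard error SD × √(2/n), so P = 2 × [1 − Φ(0.33/√(2/n))].

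- n = 23: √(2/23) = 0.295; 0.33/0.295 = 1.119; P = 0.263.
- n = 18: √(2/18) = 0.333; 0.33/0.333 = 0.990; P = 0.322.

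**Chance of a trigger, binary variable.** Exact binomial enumeration of relative risk 2 or more in either direction, with pooled prevalence of at least 10%, at 23 per arm:

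| True prevalence | P(trigger) |
|---|---|
| 10% | 0.22 |
| 15% | 0.34 |
| 20% | 0.32 |
| 30% | 0.19 |
| 40% | 0.09 |
| 50% | 0.04 |

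**Chance of at least one trigger.** Six listed variables are continuous: age, BMI, ABPI, ankle circumference, calf circumference and ankle mobility. If they are independent, 1 − (1 − 0.263)⁶ = 0.84 at 23 per arm. Adding ten binary variables (assumed independent, prevalences 15% to 50%), simulation gives about 4 triggers on average (5th to 95th percentile 1 to 7) and at least one in about 99% of trials. Independence and the prevalences are assumptions; the document gives neither.

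**What pre-specified adjustment could gain.** The document gives no R² for log(Area2/Area1), so a range is needed. The 71% v 22% contrast gives one rough anchor:

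- Two groups split 50:50: R² = (0.49/2)²/(0.465 × 0.535) = 0.24.
- Split 90:10: overall rate 0.661; R² = 0.9 × 0.1 × 0.49²/(0.661 × 0.339) = 0.10.

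With residual SD = 0.5 × √(1 − R²) and 18 per arm, the normal approximation gives 84% at R² = 0.10 and 90% at R² = 0.24, against 80% unadjusted.

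A stricter calculation uses t with 34 − k degrees of freedom for k added terms. It also inflates the standard error by √(35/(35 − k)) for chance correlation of those terms with treatment.

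- R² = 0.10, k = 5: noncentrality 2.97/1.080 = 2.75; power about 76%.
- R² = 0.24, k = 2: noncentrality 3.23/1.030 = 3.14; power about 86%.

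The range is about 76% to 86%, against 78% unadjusted. At the low end nothing is gained.

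**The case against.** The strongest reply is that the plan is ordered: the unadjusted analysis comes first and the covariate model is called a second one. A reader might infer an inflated type I error or two rival primary results. The text does not support that. The first analysis keeps its error rate, and leaving out prognostic strata makes it conservative, not invalid. What remains is lost precision and no explicit statement of which result decides.

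Second, the article is condensed and is silent on covariates in the first regression, so a separate analysis plan could put the strata there. That is fair. The criticism here rests on the printed rule, which fixes a list, thresholds and a selection mechanism. Nor is it an error in itself that site and wound size are absent from an imbalance list, since stratified blocks of 2 and 4 already balance them. Analysing log(Area2/Area1) also expresses the outcome relative to baseline area, though this does not replace adjusting for it.

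Third, a reader might take 71% v 22% as support for a power of 88% to 90%. It is not. The contrast sets two extreme groups against each other, concerns complete healing at 24 weeks and not area ratio at 12 weeks, needs an assumed split, and leaves out degrees of freedom.

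Fourth, the trigger frequencies depend on assumptions. BMI, ankle and calf circumference are plausibly correlated, and medication history is not one defined binary variable. The per-variable rate of 26% does not depend on this.

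Finally, this is a pilot meant to estimate variability and recruitment. That limits the consequence but does not remove it, because the plan also tests the primary outcome at p = 0.05.

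**Conclusion.** The concern holds in a limited form. The printed rule makes the adjusted model's covariates a matter of chance: about 26% per continuous variable at 23 per arm (32% at 18), 4% to 34% per binary variable depending on prevalence, and about 84% for at least one trigger from six continuous variables if independent. The list leaves out ulcer area and duration, which the protocol names as prognostic, and no adjustment for the strata is stated. The unadjusted first analysis remains valid but is conservative and less precise where the strata predict outcome, and precedence between the two results is not stated.

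The size of any power gain is unknown. Under an assumed R² of 0.10 to 0.24 it runs from none to several percentage points once degrees of freedom are counted. The case for change rests on having one pre-specified answer based on prognosis, and not on a claimed increase in power.

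**What to change.** Replace the imbalance trigger with one small pre-specified adjusted primary model for log(Area2/Area1): treatment, log baseline area (or the wound-size stratum), and site with small sites pooled. Add log ulcer duration only if it is recorded: the inclusion criteria require at least 4 weeks, but the assessment sections do not list exact duration as a data item. State that this model decides, and report the unadjusted result as a sensitivity analysis. Show the other baseline variables descriptively. If ranks are needed, use a stratified rank test in place of the plain Wilcoxon test.

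The cost is wording plus a few degrees of freedom, which matter with 36 to 46 participants, so the covariate set must stay small. Baseline area and site are already collected; recording of duration should be confirmed before it is written into the model.

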### Criteria for Participant Withdrawal

Participants will be advised that they may withdraw from the study at any time, for any reason, or if necessary, the Investigator may withdraw a study participant to protect their health. Study participants may also be withdrawn for not complying with study procedures such as not wearing compression bandages. The reasons for withdrawal will be fully documented in the study participants notes and CRF. Participants who are withdrawn or drop out of the randomised treatment will be allocated for continuing follow up care to the specialty wound clinic for wound management. All adverse events will be documented and the reasons for withdrawal ascertained wherever possible.

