### Plan and Trial Design

This pilot study is a randomised, multi-centre clinical trial to evaluate the efficacy and safety of graduated three layer straight tubular bandaging (intervention arm) compared with standard compression therapy (control arm) in participants with chronic venous ulceration. Neither participants nor study staff will be blinded to treatment. Screening evaluations will ensure that potential participants fulfil all requirements for entry into the study. Forty six study participants will be randomised (1:1) to either intervention arm or to the control arm of the study. Study participants will be reviewed weekly during the 12 week treatment period, and if healed in treatment period, participant will be also be reviewed monthly for three months during a subsequent follow up period.

In the following sections, a detailed description of all study procedures is given. All study visits and procedures are described and the evaluations performed at each visit are detailed. An overview and schedule of the visits and procedures is provided in Table 1.

**Table 1 T1:** Study Schedule

		Screening Period		Treatment Period Weeks													Follow-Up Period Months		
	
		Screening visit		Day 1	1	2	3	4	5	6	7	8	9	10	11	12	Month1	Month2	Month3
Informed Consent		X																	

Inclusion Criteria		X																	

Exclusion Criteria		X																	

Randomisation		X																	

Medical history		X																	

Physical Examination		X														X	X	X	X

Vital Signs		X		X	X	X	X	X	X	X	X	X	X	X	X	X	X	X	X

Intercurrent Illness		X		X	X	X	X	X	X	X	X	X	X	X	X	X	X	X	X

Intercurrent Medication		X		X	X	X	X	X	X	X	X	X	X	X	X	X	X	X	X

Tolerability Assessment				X	X	X	X	X	X	X	X	X	X	X	X	X	X	X	X

Target ulcer assessment		X		X	X	X	X	X	X	X	X	X	X	X	X	X	X	X	X

SF 36 and CWIS				X												X			X

Adverse events				X	X	X	X	X	X	X	X	X	X	X	X	X	X	X	X

Compression hosiery fitting/ application		X														X^2^			

Check for Ulcer Recurrence																	X	X	X

Care of ulcer information sheet		X														X^2^	X^4^	X^4^	X^4^

Referred back to specialty wound clinic																X^3^	X^4^	X^4^	X^4^

X^2^: If healed.

X^3^: If not healed.

X^4^: If ulcer has recurred.

*: If target ulcer has completely healed, (defined as 100% epithelialisation with no presence of exudate or scab).

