### Sample Size and Analysis plan

Participants will be randomised to graduated three layer straight tubular bandaging system (3L) or to a standard short stretch compression bandaging system. From a previous study [25] we anticipate an average reduction of 20% in wound size from baseline to follow-up in the group that receives 3L. To detect with 80% power a difference in the mean percentage reduction of 50% in the group with standard compression versus 20% in the 3L group requires 18 participants per group. This assumes a two-sided z-test (alpha = 0.05) of mean log (Area2/Area1) where Area2 is the area of the wound at follow-up and Area1 is the area of the wound at baseline. Percentage reduction is defined as 100(Area2-Area1)/Area1 and percentage reductions of 20% and 50% correspond to a difference in means of 0.47 on the scale of analysis (log(Area2/Area1)). From a previous study (Vowden et al, 2007) we estimate the standard deviation of log(Area2/Area1) to be 0.5 in each group. If a wound has completely healed and Area2 = 0 then we will use log (min (Area2)/Area1) in analysis where Area2 = Area1/100 is the smallest observed wound area at follow-up among those participants whose wounds did not completely heal. A two-sided p-value of 0.05 will be considered to be statistically significant.

With 18 participants per group the study will have 55% power to address the secondary endpoint of complete healing if the effect of standard compression is to improve the rate of healing from 20% of participants fully healed (with 3L) to 60% with standard compression.

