### Pilot study sample size justification

We will recruit 46 participants in total to enable the estimation of the between-person variability in percentage reduction in wound size from baseline to 12 weeks. There are insufficient previous studies to ascertain a likely value for this variability for use in power calculations for a fully powered trial.

The analysis principle for the primary outcome will be Intention-to-treat. The data will be analysed according to the treatment group to which participants are randomised even if they do not comply fully with their treatment. If participants drop out of the study they will be asked if they would still be prepared to return at the 12 week end of treatment schedule for target ulcer measurement.

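### As written, the intention-to-treat primary test scores only participants with a week-12 ulcer area (planned as 18 of 23 per arm), so loss that is both unequal and related to ulcer course would shift it.

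*Protocol article*

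**What the plan says.** All references are to the protocol article.

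- **Test and target** (Sample Size and Analysis plan). The calculation is made "To detect with 80% power a difference in the mean percentage reduction of 50% in the group with standard compression versus 20% in the 3L" arm. On the test: "This assumes a two-sided z-test (alpha = 0.05) of mean log (Area2/Area1"), where Area2 is the follow-up area and Area1 the baseline area. The analysis is a z-test and linear regression, or a Wilcoxon rank-sum test if the log ratio is not reasonably symmetric. A healed ulcer (Area2 = 0) receives a substitute value. No value is given for an Area2 that was not measured.
- **Numbers** (same section). "18 participants per group need to have wound area assessed at the end of the 12-week follow-up". Then: "To allow for loss-to-follow-up of 20% of participants between baseline and follow-up we will randomise 23 participants to each arm".
- **Principle** (Pilot study sample size justification). "The analysis principle for the primary outcome will be Intention-to-treat". This is explained as analysis by randomised group despite incomplete compliance. Drop-outs will be asked whether they would come back for the week-12 measurement.
- **Healing** (Secondary Outcomes; Sample Size and Analysis plan). The outcome is the proportion healed at any time in the trial. Its power is also quoted on the smaller number: "With 18 participants per group the study will have 55% power to address the secondary endpoint of complete healing". No denominator for the analysis is stated.
- **Data collected** (Table 1). Target ulcer assessment takes place at screening, on Day 1 and at every weekly visit to week 12.
- **Withdrawal.** "Participants will be advised that they may withdraw from the study at any time, for any reason" (Criteria for Participant Withdrawal). The investigator may also withdraw people for not wearing the bandage. Withdrawals are the measure of acceptability under Secondary Outcomes.

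**The concern.** The test, the data it needs, the effective sample size and the analysis principle do not fit together. A log ratio with Area2 at week 12 cannot be formed for someone who has no week-12 area. An analyst who followed the article literally would compare the measured participants and label the result intention-to-treat.

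That matters here because loss need not be alike in the two arms. The trial is open label, and withdrawal is itself an outcome. The Background links non-adherence to pain and discomfort and presents the tubular system as better tolerated. If people whose ulcers are doing badly leave one arm more often, that arm's remaining participants look better than the arm as randomised. The pilot's estimates are meant to inform a larger trial, so any distortion would be carried into its design.

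Meanwhile the areas recorded each week before a participant leaves, which say how that ulcer was progressing, play no part in the stated primary analysis.

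**Working it through.** **1. The plan's own figures reproduce.**
- Difference on the log scale: ln 0.8 − ln 0.5 = 0.470. SD 0.5, two-sided alpha 0.05, power 80%.
- n per group = 2 × (1.960 + 0.842)² × 0.5² / 0.47² = 17.8, so 18. Power at 18 is 80.5%.
- Allowance for 20% loss: 18 / 0.8 = 22.5, so 23 per arm and 46 in total.
- Conversely, 23 × 0.8 = 18.4. If loss reaches the allowance, about 5 of 23 per arm (21.7%) have no week-12 area.
- Healing power at 18 per group for 20% v 60%: 70.4% (pooled z), 61.4% (Fisher exact), 56.5% (continuity-corrected z). The stated 55% is close to the last.

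**2. When the comparison of measured participants shifts.** Let drop-outs have a mean log ratio g worse (higher) than stayers, and let d be the proportion lost. The arm mean is stayer mean + d·g, so the stayers' mean is too favourable by d·g. The arm difference is therefore off by g × (d₂ − d₁). It is zero if g = 0 or if d₁ = d₂ with the same g. Both conditions, unequal loss and outcome-related loss, are needed.

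Illustration with no true effect, 23 per arm and SD 0.5. The value of g is an assumption, shown over a range. Loss of 2 v 7 gives d₂ − d₁ = 5/23 = 0.217, and SE = 0.5 × √(1/21 + 1/16) = 0.166.

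| g | shift | share of 0.47 | type I error |
|---|---|---|---|
| 0.25 | 0.054 | 12% | 6.2% |
| 0.5 | 0.109 | 23% | 10.0% |
| 1.0 | 0.217 | 46% | 25.8% |

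For 3 v 6 the shift is 0.03 to 0.13 and the type I error 5.4% to 12.4%. For 5 v 5 the shift is 0.

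**3. Simulation under the plan's effect.** Inputs from the plan: means ln 0.8 and ln 0.5, SD 0.5, 23 per arm. Assumed: linear trajectories, measurement SD 0.15, and drop-out at week 6 more likely in poorly progressing ulcers (logistic slope 1.5 per SD).

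| Loss, 3L / short stretch | Difference in those measured | Power |
|---|---|---|
| 20% / 20% | 0.47 | – |
| 30% / 10% | 0.39 | 70% |
| 10% / 30% | 0.55 | 93% |

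The shift is about 0.08 / 0.47 = 17% in either direction. With no true effect, the two unequal patterns give about 9% type I error. A small part of the excess over 5% comes from using a normal reference with an estimated SD in groups of this size.

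Predicting week 12 from the week-6 area returned 0.46 to 0.47 in all three patterns.

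**4. A by-product for the pilot's aim.** Under the same assumed mechanism, balanced 20% loss lowers the SD among those measured from 0.50 to about 0.47. Since (0.47 / 0.50)² = 0.88, a sample size built on it would be about 12% too small.

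**The case against.** Missing-data methods are commonly left to the analysis plan or full protocol, neither of which is shown, so the absence of a policy is not itself an error. Powering on the number expected to be measured and inflating for loss is routine. The 20% is a planning allowance, and the plan tries to retrieve drop-outs at week 12. All of this stands. What remains is narrower: the article does fix the test, its data and its principle, and these give a comparison of those measured unless something is added. Retrieval reduces the number missing but does not say how the rest are handled.

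The drop-out timing, slope and splits are assumptions found nowhere in the documents. The simulation also favours the week-6 prediction, because drop-out was made to depend on that value. In addition, SD 0.5 sits badly with healing of 20% and 60% if healed ulcers score Area1/100 (ln 0.01 = −4.6), so the power figures are illustrative only. In a rerun with that healed score, the week-6 area still removed most of the bias and lowered the error.

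Two stronger readings are tempting and not supported:
- *Healing is analysed on 18 per group.* The 18 appears only in a power statement. Healing counts at any time in the trial and is checked weekly, so all 23 per arm can be scored, and intention-to-treat is named only for the primary outcome.
- *A fifth of participants will be discarded and the result will be biased.* The fifth is an allowance, and balanced loss leaves the difference essentially unchanged.

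Participant Compliance also says that protocol deviators may be ineligible for analysis. That sits uneasily with intention-to-treat but is a separate matter, not relied on here.

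**Conclusion.** The point holds in limited form and should be corrected. The primary analysis as written uses only participants with a week-12 area, planned as 18 of 23 per arm, under an intention-to-treat label whose only provision for drop-outs is an invitation to return. Whether this biases the result depends on facts not yet known: loss must be both unequal between bandages and related to ulcer course. That is plausible in this open-label trial but not established. Under the assumed 30%/10% and 10%/30% patterns, 0.47 becomes about 0.39 or 0.55 with about 9% type I error. With balanced loss the effect on the difference is negligible. No error is found in the sample-size arithmetic. For healing, the only step needed is to state the denominator.

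**What to change.** In Sample Size and Analysis plan and Pilot study sample size justification:

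1. **Primary.** Estimate the week-12 difference in all randomised participants with a post-baseline area, using the weekly log(area/baseline area). Use either a repeated-measures model or imputation of week 12 from the earlier weekly areas.
2. **Early healing.** Participants who heal early leave the weekly visits for monthly follow-up (Treatment Period - Early Completion). State that ulcers healed before week 12 are carried to week 12 with the plan's healed score.
3. **Sensitivity analyses.** Keep the week-12-only test. Add a rank-based comparison in which drop-outs with neither recorded healing nor a week-12 area take the worst rank.
4. **Healing.** State that the denominator is all randomised participants, that healing at any weekly visit counts, and that drop-outs without recorded healing count as not healed. Say that 18 per group is a power input, not the analysis set.

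The cost is wording and modest extra programming, with no added visits, measurements or participants. The primary estimate would rest on a missing-at-random assumption, namely that drop-outs resemble others with the same ulcer course so far. Healed scores far below the other values may suit a normal model poorly in 46 people, which is a reason to keep the rank-based analysis alongside. Reported healing rates would be slightly lower than among completers, and counting drop-outs as not healed is itself a convention that unequal loss can affect.
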